**Methods and analysis:**

We are undertaking an international multicentre, double-blind, placebo-RCT to evaluate whether 12 months of erdosteine is beneficial for children and adults with bronchiectasis. We will recruit 194 children and adults with bronchiectasis to a parallel, superiority RCT at eight sites across Australia, Malaysia and Philippines. Our primary endpoint is the rate of exacerbations over 12 months. Our main secondary outcomes are QoL, exacerbation duration, time-to-next exacerbation, hospitalisations and lung function.

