### Study settings and participants

#### Study sites

Our current study sites are across three countries: Australia, Malaysia and the Philippines. The Australian sites are Queensland Children’s Hospital (Brisbane), Mater Hospital (Brisbane), Concord Repatriation Hospital (Sydney), Perth Children’s Hospital (Perth), Royal Darwin Hospital (Darwin) and Gold Coast University Hospital (Gold Coast). The Malaysian site is the University of Malaya Medical Centre (Kuala Lumpur) and in the Philippines, children are recruited from St Luke’s Hospital (Quezon City). Adults are recruited only from the Mater and Concord Repatriation Hospitals.

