#### Inclusion criteria

Inclusion criteria are as follows: (1) Children or adults aged 2–49 years, (2) have radiographic-confirmed bronchiectasis with at least two exacerbations or one hospitalisation for an acute respiratory exacerbation in the last 18 months and (3) are able to be contacted for the 15-month follow-up period.

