#### Randomisation, allocation concealment and blinding

Randomisation is undertaken by each study site’s pharmacy using REDCap where the sequence is stratified by site in permuted blocks sizes of 4–8. Allocation is thus undertaken by the local hospital pharmacist (or representative) who then dispenses the trial medications to the participant. Trial medications are dispensed every 3 months and adherence is monitored by return of bottles, collection of study medications and parent reports.

People who are blinded to treatment allocation are (1) receiving the treatment, (2) administering the treatment, (3) assessing the outcomes and (4) analysing the results/data.

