#### For the primary aim

To assess erdosteine efficacy, the exacerbation rate in those randomised to receive erdosteine will be compared with controls (receiving placebo). We will use a negative binomial regression model (as recommended,^46^ including treatment group, and number of months in the study included as an offset) to determine between-group differences (with 95% CI), as done previously.^19^

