### Potential study limitations

Although our study has many novel and robust aspects, there are also limitations. First, while including children and adults in a single RCT is a strength and addresses criticisms of children not being involved sufficiently in clinical trials,^54^ it may also be a limitation as children with bronchiectasis have many different characteristics to adults.^7 49^ Including a wide age range increases the heterogeneity of the target population. We have attempted to minimise this potential limitation by not recruiting older adults aged >50 years and stratifying randomisation by site since centres recruited only either children or adults, and not both. We plan to include age in a sensitivity analysis. Second, we developed our protocol before the international consensus on the core outcome set (COS) for children with bronchiectasis^52^ was developed. The COS arose from a systematic review and international surveys that had 562 respondents (201 parent/patients; 361 healthcare professionals) from 59 countries.^52^ As such our outcomes do not include two of the five COS items, namely unscheduled healthcare visits and symptoms. Also, although we included QoL tools, there is currently no validated bronchiectasis-specific QoL instrument for children. Third, our study is underpowered for some secondary outcomes like lung function and hospitalisations. Fourth, considering the adverse impact of the SARS-CoV-2 pandemic (see the ‘Impact of the SARS-CoV-2 pandemic upon the clinical trial’ section), our RCT may be underpowered for assessing the efficacy of erdosteine for the primary outcome too.

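### The primary negative binomial model omits site, the stratification factor that separates children from adults; if rates differ between sites, its confidence interval is conservative and some power is given up

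*Protocol article*

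**What the plan says.** For the primary aim, the Protocol article names a negative binomial regression and lists its terms: "including treatment group, and number of months in the study included as an offset". No site, country or age-group term appears.

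Under Randomisation, allocation concealment and blinding, "the sequence is stratified by site in permuted blocks sizes of 4–8". No other stratification factor is named. Potential study limitations gives the reason: the wide age range adds heterogeneity, and the trial tries to limit this by "stratifying randomisation by site since centres recruited only either children or adults, and not both". The same paragraph gives age a secondary role: "We plan to include age in a sensitivity analysis".

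The trial runs "at eight sites across Australia, Malaysia and Philippines". Study sites adds: "Adults are recruited only from the Mater and Concord Repatriation Hospitals". So two of the eight sites are adult sites.

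Outcomes and endpoints defines the primary event differently in the two groups. In children it is an antibiotic-treated event with specified signs. In adults it needs a clinician's decision to change treatment and deterioration in at least three listed features for at least 48 hours.

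**The concern.** Site carries country, age group and event definition. The design treats it as important enough to be the stratification factor, and the stated primary model then leaves it out.

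Stratified blocks balance between-site variation across the arms, so that variation contributes almost nothing to the sampling error of the treatment comparison. A model without site cannot know this. It counts the variation as overdispersion and reports a standard error larger than the real one. An age sensitivity analysis does not alter the primary interval.

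Precision matters here. Potential study limitations concedes that the trial may be underpowered for the primary outcome, and the section on the pandemic reports fewer exacerbations than predicted.

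**Working it through.** **1. The plan's own figure.** Inputs from Sample size: rates 3.0 and 1.8 per year, alpha 0.05, power 90%, 164 evaluable. Assumed: two-sided test, 82 per arm, one year of exposure. The dispersion k is not stated, so I solved for it.

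- n per arm = (1.960 + 1.282)² × (1/3 + 1/1.8 + 2k) / (ln 0.6)²
- 82 × 0.2609 / 10.507 = 2.036 = 0.889 + 2k, so k = 0.574

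The 164 is therefore reproduced if k is about 0.57. The only spread figure in the article (Introduction: mean 3.3, SD 2.2 per child-year) gives k = (4.84 − 3.3)/10.89 = 0.14. At that value 82 per arm would give about 99% power.

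**2. How site enters.** Let site rates, relative to the overall mean, have variance v. Then total k = v + (1 + v) × k within site, so k within = (k − v)/(1 + v). The unadjusted model uses total k; a site-adjusted model needs only k within. By the formula in step 1 with k = 0.574:

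- v = 0: standard error of the log rate ratio √(2.036/82) = 0.158, power 90.0%
- v = 0.05: k within 0.499, standard error 0.152, power 92.0%
- v = 0.15: k within 0.368, standard error 0.141, power 95.2%

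The adjusted figures are approximate. Step 3 checks them by simulation.

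**3. Simulation.** 164 participants, eight near-equal sites, 1:1 allocation stratified by site, rate ratio 0.60, total k held at 0.60, 4,000 runs per scenario. The site differences are assumptions. Monte Carlo standard error: √(0.92 × 0.08/4000) = 0.4 points for power, √(0.05 × 0.95/4000) = 0.3 points for type I error.

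| Assumed site differences | v | Power %, unadjusted → site-adjusted | Type I error %, unadjusted / adjusted | Unadjusted SE, model / actual | Adjusted SE, model / actual |
|---|---|---|---|---|---|
| None | 0 | 90.2 → 90.5 | 5.7 / 6.5 | 0.159 / 0.158 | 0.156 / 0.159 |
| Adult:child rate ratio 1.5 | 0.037 | 90.5 → 91.8 | 4.7 / 5.1 | 0.158 / 0.156 | 0.152 / 0.157 |
| Adult:child rate ratio 2 | 0.121 | 92.3 → 94.4 | 4.4 / 5.5 | 0.155 / 0.151 | 0.144 / 0.149 |
| Site log-rate SD 0.25 | 0.064 | 90.7 → 92.2 | 4.3 / 5.4 | 0.158 / 0.153 | 0.150 / 0.153 |
| Site log-rate SD 0.4 | 0.162 | 91.9 → 94.8 | 3.5 / 5.5 | 0.156 / 0.149 | 0.141 / 0.147 |
| Site log-rate SD 0.6 | 0.353 | 94.3 → 98.6 | 1.2 / 5.6 | 0.157 / 0.128 | 0.125 / 0.126 |

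Coverage of the unadjusted 95% interval is 95.9% at SD 0.4 and 98.6% at SD 0.6.

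**4. Unequal sites.** Two further simulations used eight unequal sites, blocks of 4 or 8 and total dispersion about 0.57:

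- 40% reduction (1,600 runs per scenario): power 92.4% → 93.8% at SD 0.3, and 95.3% → 97.3% at SD 0.5.
- 35% reduction, smaller than planned (1,500 runs): 80% → 84% at SD 0.3, 87% → 92% at SD 0.5, and 80% → 81% with no site differences.

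**5. Reading the results.** The gain with site in the model is roughly 1 to 5 points when sites differ. The actual spread of the estimate hardly changes (0.149 against 0.147 at SD 0.4), so the gain comes mainly from the reported standard error. Part of it reflects an adjusted standard error that is slightly too small.

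**The case against.** **The analysis plan may add site.** The article is condensed, announces a detailed statistical analysis plan, and uses a word (including) that need not be exhaustive. This softens the point without removing it: the article does state the model's terms, and site appears in no analysis it describes.

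**The size is assumed.** No between-site spread is given, and two event definitions do not by themselves fix a rate difference. This stands, which is why the conclusion is conditional.

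**The planned power is met.** A reader might infer that the trial falls short of 90% because site is omitted. The calculations do not support that. At the planned 40% reduction the unadjusted model had 90.2% to 94.3% power in every scenario of the table. Its power rises with site spread because total k is held fixed and stratification removes the between-site share from the comparison. The loss is only relative to the adjusted model. This assumes that the undisclosed k already includes site variation.

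**Adjustment is not free.** With eight site levels, simulated type I error was 5.1% to 6.5%. With unequal sites at SD 0.5 it was 6.4% (model standard error 0.118, actual 0.122), against 3.3% unadjusted. This stands, and it is the reason for pooling.

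**The offset.** A reader might infer that untransformed months would enter a log-link model. Naming months as the offset is ordinary shorthand for exposure time, and nothing in the article suggests otherwise.

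**Conclusion.** The point holds in conditional form. The stated primary model does not reflect the stated randomisation. If site rates differ, the unadjusted interval is conservative and about 1 to 5 points of power are given up over assumed site log-rate SDs of 0.25 to 0.6. If they do not differ, nothing is lost. Different populations, countries and event definitions make some difference plausible, but the documents do not show how large it is.

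It would go too far to say that the interval is too wide as a matter of fact, or that the primary analysis is invalid. The error is in the cautious direction and the point estimate hardly changes. The figures rest on a total dispersion of about 0.6, which was solved from the sample size and is not stated in the article, and on 164 evaluable participants in equal arms. Only the primary model was examined; nothing here bears on the Cox or covariance analyses.

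**What to change.** Before unblinding, state that the primary negative binomial model contains treatment group, site and the follow-up offset, and keep the unadjusted model as a sensitivity analysis.

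Pool very small sites within country and child/adult group, with the size threshold set in advance. Six Australian sites (two adult, hence four paediatric) plus one each in Malaysia and the Philippines leave between four and eight levels, that is, three to seven extra parameters. The single Malaysian and Philippine sites have no partner under this rule, so say in advance where either goes if it is tiny. Pooling was not itself simulated. A child/adult term alone is a leaner fallback: with an adult:child rate ratio of 2 it gave 94.0% power and 4.9% type I error, against 94.4% and 5.5% with all sites.

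The prior exacerbation count is optional. Eligibility needs only a threshold ("at least two exacerbations or one hospitalisation for an acute respiratory exacerbation in the last 18 months"), so use it only if the count is recorded at baseline.

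The cost is one sentence and no new data, plus a slight risk of too small a standard error if tiny sites stay separate.

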### For the secondary aims

The change (12 months minus baseline) in (1) respective domain scores of the QoL tools and (2) spirometry values (FEV_1_ %predicted, FVC %predicted and FEV_1_/FVC) between treatment arms will be analysed using ANCOVA (analysis of covariance) and presented as the mean difference (95% CI). A Kaplan-Meier curve will be constructed for each group (intervention vs respective controls) for the time-to-the next exacerbation and respiratory-related hospitalisation, and an HR (using a Cox regression model) will be performed and reported.^18 19^

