#### Data and sample collection, monitoring and follow-up details

All collected data are recorded by GCP-trained researchers using standardised data sheets or online surveys (similar to our previous RCTs).^18 19 42^

At enrolment, sociodemographic/clinical data, spirometry (in those aged >6 years) and specimens (sputum and blood where possible in a subset of participants contributing to the discovery component) are collected (table 1).

**Table 1 T1:** Schedule for visits and contact points

Visit type	Baseline	Month												
		1	2	3	4	5	6	7	8	9	10	11	12	Start of exacerbation (if possible)
Screening for eligibility	√													
Informed consent (paper or electronic)	√													
Randomisation	√													
Medical history	√													
Medical chart review	√			√			√			√			√	
Monthly parent/participant contact recording exacerbations		√	√	√	√	√	√	√	√	√	√	√	√	
Clinical assessment (where possible)	√			√			√			√			√	√
PC-QoL-and/or QoL-B questionnaire	√						√						√	√
Spirometry (if possible)	√			√			√			√			√	√
Urine pregnancy test (only females ≥14 years	√						√						√	
Study diary	√						√						√	√
Blood in subgroup	√													√
Sputum in subgroup	√													

B-QoL, bronchiectasis QoL tool; PC-QoL, Parent-proxy Cough QoL-8 instrument; QoL, quality of life.

Sociodemographic data include details of age, gender, family and household size, cigarette smoking, family and immunisation history, medications and comorbidities. These are obtained from the carers/participants and/or reviewing the medical notes. Participants are contacted every month via electronic communication (email or short-message service texting) or by telephone to monitor progress and adverse events (eg, vomiting, diarrhoea, rash) and economic data (eg, medical visits, treatments, other interventions, school/work absenteeism). Participants are seen in the clinic 3–4 monthly as part of their routine clinical care (if they reside locally at one of the study sites) and at the onset of their first exacerbation following enrolment where additional clinical data and biological specimens are collected (table 1), if possible. Specimens will be stored and analysed later. We have established robust methods for capturing respiratory exacerbations.^18 19 43^ Hospital records are also reviewed for hospitalisations. Additionally, at enrolment, a pregnancy test is undertaken if a female participant is aged ≥14 years.

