### Data monitoring, management and analyses

All identifiable information on study participants will be retained in password-protected files stored on the QUT server or locked cabinets/rooms at study sites. Access to this information will only be provided to immediate study staff unless required by legislative or regulatory agencies and the HRECs. The principal investigator and statisticians will have access to the final trial dataset.

All adverse events, including serious adverse events, are monitored by an iDMC, which was established prior to commencing the study. An Indigenous (First Nations) Reference Group based at the Menzies School of Health Research (Darwin) oversees the cultural aspects of the study. Data coding and entry are coordinated in Brisbane and conducted in accordance with GCP.

The analyses will be directed by biostatisticians ([name] and [name]). Results will be reported and presented in accordance with Consolidated Standards of Reporting Trials guidelines. We will use the ‘intention-to-treat’ approach for the main analyses. We also plan a ‘per-protocol’ analysis. Missing data will not be imputed. No interim analysis is planned. A detailed statistical analysis plan will be developed and approved by the chief investigators and the iDMC before undertaking the final analysis. Any exploratory, post hoc or unplanned analysis will be identified clearly. Analysis code will be written and agreed on knowledge of treatment allocation and adherence is provided to the statistician, as done previously.^18 43^

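### QoL and spirometry are analysed only in participants with a month-12 value and scheduled interim values go unused; the possible bias is modest, of unknown direction, and cheap to guard against

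*Protocol article*

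**What the plan says.** Under the heading For the secondary aims, the protocol article fixes both the endpoint and the model: "The change (12 months minus baseline) in (1) respective domain scores of the QoL tools and (2) spirometry values", compared between arms, "will be analysed using ANCOVA (analysis of covariance) and presented as the mean difference (95% CI". The section Data monitoring, management and analyses adds two general rules: "We will use the ‘intention-to-treat’ approach for the main analyses" and "Missing data will not be imputed". It also announces a later document: "A detailed statistical analysis plan will be developed and approved by the chief investigators and the iDMC before undertaking the final analysis".

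Table 1 shows what is collected. The row "PC-QoL-and/or QoL-B questionnaire" is ticked at baseline, month 6 and month 12. The row "Spirometry (if possible" is ticked at baseline and months 3, 6, 9 and 12. Both rows are also ticked at the start of an exacerbation. At enrolment the text limits "spirometry (in those aged >6 years", although the trial enrols from age 2. No analysis described in the article uses the interim values of either outcome.

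The Sample size section gives 194 enrolled, endpoint data from 164, an attrition allowance of 25%, and 90% power for a QoL difference of 0.5 SD.

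**The concern.** A change to month 12 cannot be calculated without a month-12 value, and the article rules out imputation. The two statements therefore make this a complete-case analysis: a participant with a month-6 QoL score, or with three interim spirometry results, contributes nothing if month 12 is missing. This follows from what the article states, not from a detail left open.

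The interim values carry information about who leaves. If people with low scores leave one arm more than the other, the remaining groups are no longer comparable at month 12, and the ANCOVA does not use the measurement that would show it. Such a difference is conceivable here, because the exit criteria include intolerance and severe study-related adverse events, which can differ between active drug and placebo. The article does not say that it will happen. QoL matters most, because the Discussion names it with exacerbations as a main outcome and power is claimed for it.

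**Working it through.** **1. The plan's QoL power.** Inputs: 164 evaluable, difference 0.5 SD, two-sided alpha 0.05 and 1:1 allocation (sidedness and ratio are assumed). Power = Φ(0.5 × √(82/2) − 1.96) = Φ(3.20 − 1.96) = 89.3%. The stated 90% is reproduced within rounding.

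**2. How much loss.** 1 − 164/194 = 30/194 = 15.5%. A 25% allowance on 164 would need 164/0.75 = 219 enrolled. If 25% of 194 are lost, 194 × 0.75 = 145.5 remain, and QoL power by the same formula is 85.3% (145) to 85.6% (146). Depending on which figure is meant, about 30 to 49 participants would lack endpoint data. The article gives no separate figure for QoL or spirometry.

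**3. Size of the bias.** The documents give no correlations or drop-out mechanism, so everything here is assumed: 194 participants, one scale, true month-12 difference 0.50 SD growing linearly, correlation 0.5 or 0.7 (exchangeable, or decaying per 6 months), and 1,500 runs per setting. The baseline drop-out hazard per interval is 1 − 0.75^(1/K), with K = 2 intervals for QoL and 4 for spirometry. Drop-out is logistic in the previous score: slope 0 in both arms, −0.7 in both arms, or −1.0 in placebo only. Complete-case ANCOVA is compared with a sequential-regression estimator of likelihood type that uses the interim visits. Monte Carlo error is about 0.16/√1500 = 0.004.

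| Drop-out | Outcome | Without month 12 | Complete-case ANCOVA | Using interim visits |
|---|---|---|---|---|
| Unrelated to score | QoL | 25% | 0.495–0.499 | 0.495–0.499 |
| Unrelated to score | Spirometry | 25% | 0.500–0.511 | 0.499–0.511 |
| Related alike in both arms | QoL | 27% | 0.490–0.499 | 0.495–0.502 |
| Related alike in both arms | Spirometry | 27% | 0.491–0.496 | 0.498–0.503 |
| Low scorers leave placebo only | QoL | 28% | 0.443–0.471 | 0.494–0.508 |
| Low scorers leave placebo only | Spirometry | 28–29% | 0.403–0.454 | 0.498–0.505 |

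Two further sets of assumptions for QoL, with less loss, show that the sign can reverse:

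- 14–23% missing, with drop-out after month 6 tied to the month-6 score in one arm: ANCOVA 0.52–0.54, likelihood estimate 0.49–0.50. With score-related drop-out in both arms, ANCOVA gives 0.48–0.49.
- About 20% missing, 97 per arm, one-arm drop-out: ANCOVA 0.54–0.55 or 0.46, likelihood estimate 0.50. With drop-out random or alike in both arms, ANCOVA gives 0.49–0.50.

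**4. Bias against noise.** With 146 evaluable and baseline correlation ρ, SE = √(1 − ρ²) × 2/√146, which is 0.143 at ρ = 0.5 and 0.118 at ρ = 0.7. A QoL bias of 0.05 is then 0.05/0.143 = 0.35 to 0.05/0.118 = 0.42 of a standard error. In the worst QoL setting of the table, the bias is 0.50 − 0.443 = 0.057, or 0.057/0.151 = 0.38 of the simulated standard deviation. For spirometry the largest bias is 0.50 − 0.403 = 0.097, or 0.097/0.161 = 0.60.

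**5. Precision.** The variance ratio of ANCOVA to the estimator using interim visits ran from 0.999 to 1.085, so the efficiency gain is about 0 to 8%. On the standard-error scale that is at most √1.085 − 1 = 4%.

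**The case against.** The strongest reply is that the plan is coherent as it stands. Month 12 is a legitimate endpoint, ANCOVA is a standard method for a single time point, these are secondary outcomes, and the article concedes limited power for lung function. A detailed analysis plan is still to come and could adopt a repeated-measures model without breaking the no-imputation rule. All of this stands, and it keeps the point at the level of an improvement. It does not remove the point, because the article states both the model and the missing-data rule.

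A second reply is that the simulation flatters the remedy. The trial uses two QoL instruments analysed by domain, spirometry has an age limit and is done when possible, and clinic visits depend on living near a site. Someone who misses month 12 because of distance may miss the interim visits too, and no model recovers a participant with no post-baseline values. This also stands.

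Several stronger readings are tempting but unsupported:

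- That the ANCOVA is unbiased only if loss is unrelated to interim scores. When drop-out was related alike in both arms, the estimates stayed at 0.48–0.50.
- That participants doing badly are the likeliest to leave, or that the result will favour erdosteine. The documents say neither, and the sign depends on which arm loses its low scorers.
- That the plan contradicts its intention-to-treat statement. An intention-to-treat approach can mean analysis by allocated group, and the article sets a separate per-protocol analysis beside it.
- That a quarter of participants will be lost. The section's own counts imply 15.5%, and they were set for the primary endpoint.
- That three interim visits are wasted for both outcomes. Months 3 and 9 apply to spirometry only.

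**Conclusion.** The point holds in limited form. As stated, the QoL and spirometry analyses exclude participants without a month-12 value and leave scheduled interim data unused. If drop-out is unrelated to scores or similarly related in both arms, the result is close to unbiased. If score-related drop-out differs by arm, the bias is roughly 0.02 to 0.05 SD on a 0.5 SD QoL effect (just under 0.06 in the worst setting run), in either direction, and up to 0.10 SD for spirometry. These sizes rest on assumed correlations of 0.5 to 0.7, assumed drop-out models and 14–29% missing. For QoL the bias is about a third of a standard error, so it would shift an estimate more often than overturn a conclusion. The primary analysis is not affected.

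**What to change.** In the analysis plan, make the main analysis of QoL and spirometry a likelihood-based mixed model for repeated measures on all scheduled post-baseline values: month 6 and 12 for QoL; months 3, 6, 9 and 12 for spirometry. Include treatment, visit, treatment-by-visit, baseline-by-visit and site, with an unstructured covariance. Report the month-12 contrast as the mean difference with its 95% CI, so that the endpoint and its presentation stay as they are. Keep the 12-month ANCOVA as a sensitivity analysis. In the same revision, reconcile the 25% loss with the 194 and 164, and report missing month-12 values by arm.

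No new data are needed and nothing is imputed. The cost is plan wording, slightly more analysis work and reliance on missing-at-random. Little power is gained, and participants with no post-baseline values are not helped.
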